### 2.3. Outcomes Measurement

Three evaluations will be carried out for each patient. A pre-intervention initial evaluation, a second evaluation the week following the end of the rTMS intervention, and a final evaluation after two weeks, when the NeuRow training finish. The first and third evaluation sessions will have an average duration of 120 min, and the second evaluation will have a duration of 60 min (Figure 2).

#### 2.3.1. Main Outcomes

Due to the bilateral stimulation protocol used, all outcomes will be assessed on both sides.

Motricity Index of the Arm (MI): The upper limb section of the MI assesses muscle strength in 3 muscle groups, including grip, elbow flexion, and shoulder separation. Each movement is scored discreetly (0 if there is no movement, 9 if the movement is palpable, 14 if the movement is visible, 19 if the movement is against gravity, 25 if the movement is against resistance, and 33 if the movement is normal), obtaining a total score for the upper limb that ranges from 0 (severely affected) to 100 (normal). This assessment methodology has been widely used in rehabilitation progress evaluation [44,45] and counts with a normalized and weighted scoring system.

Dynamometry: A handheld analogic dynamometer (Jamar^®^ Plus+ Hand Dynamometer, 0–90 kg) (Performance Health Supply, Nottinghamshire, UK) will be used to assess isometric grip strength. Patients will be positioned in a straight back chair with both feet on the floor and the forearm resting on a stable surface. Patients will perform a maximal isometric grip contraction until they reach maximal force output. Three measures will be taken with 1 min rest between tests, and the mean value will be recorded. This provides an objective evaluation of handgrip strength that will allow pre- and post-protocol comparison.

Fugl-Meyer Assessment for upper extremity (FMA-UE): The FMA-UE is an observational rating scale that assesses sensorimotor impairments in post-stroke patients. It also includes four subscales: A. Upper Extremity (0–36), B. Wrist (0–10), C. Hand (0–14), and D. Coordination/Speed (0–6), composing a total maximum score of 66 points. This scale is considered adequate to detect changes in motor recovery in patients who have suffered a stroke because of its wide evaluation items [46]. The minimum clinically important difference (MCID) for the upper limbs has been determined and ranges from 4.25 to 7.25 points, depending on the evaluated region of the upper limb [47].

Stroke Impact Scale (SIS): The SIS is a stroke-specific quality of life instrument to assess the quality-of-life impairment after stroke only considering the physical domain. It presents 4 subscales, but only the hand function domain will be evaluated. The SIS is a brief and easy instrument that considers specifically motor impairment impact over daily living activities [37].

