## Abstract

*Background and Objectives:* The motor sequelae after a stroke are frequently persistent and cause a high degree of disability. Cortical ischemic or hemorrhagic strokes affecting the cortico-spinal pathways are known to cause a reduction of cortical excitability in the lesioned area not only for the local connectivity impairment but also due to a contralateral hemisphere inhibitory action. Non-invasive brain stimulation using high frequency repetitive magnetic transcranial stimulation (rTMS) over the lesioned hemisphere and contralateral cortical inhibition using low-frequency rTMS have been shown to increase the excitability of the lesioned hemisphere. Mental representation techniques, neurofeedback, and virtual reality have also been shown to increase cortical excitability and complement conventional rehabilitation. *Materials and Methods:* We aim to carry out a single-blind, randomized, controlled trial aiming to study the efficacy of immersive multimodal Brain–Computer Interfacing-Virtual Reality (BCI-VR) training after bilateral neuromodulation with rTMS on upper limb motor recovery after subacute stroke (>3 months) compared to neuromodulation combined with conventional motor imagery tasks. This study will include 42 subjects in a randomized controlled trial design. The main expected outcomes are changes in the Motricity Index of the Arm (MI), dynamometry of the upper limb, score according to Fugl-Meyer for upper limb (FMA-UE), and changes in the Stroke Impact Scale (SIS). The evaluation will be carried out before the intervention, after each intervention and 15 days after the last session. *Conclusions:* This trial will show the additive value of VR immersive motor imagery as an adjuvant therapy combined with a known effective neuromodulation approach opening new perspectives for clinical rehabilitation protocols.

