### 2.1. Study Design and Participants

Participants will be recruited in the Brain Injury Unit or Rehabilitation Unit of the Beata María Ana Hospital; patients referred from other centres and self-referred patients will also be considered. The subjects included will be assessed by a neurologist ([name]) and a physiotherapist ([name]). All patients will have had a hemispheric ischemic or hemorrhagic stroke (>3 months after stroke) diagnosed in at least one brain-imaging test and presenting motor sequelae in the upper limb. We have ruled out the first three months since the phenomenon is known as “spontaneous recovery” [36] takes place in time, and therefore, it would be difficult to discern the cause of the clinical improvement that we expect from patients. The patients included in the study will have an alteration of mobility and/or functionality in the upper limb related to the stroke and with a score equal to or greater than 25 according to the Fugl-Meyer Assessment for upper extremity (FMA-UE) [37]. The rest of the specific inclusion and exclusion criteria are shown in Table 1.

The study design corresponds to a randomized, single-blind, controlled clinical trial in which patients are randomly assigned to two groups: 1. Conventional rehabilitation + bilateral rTMS + Immersive multimodal BCI-VR training system NeuRow (NeuroRehabLab, Funchal, Portugal), and 2. Conventional rehabilitation + bilateral rTMS.

Regarding adherence strategies, sessions missed up to the established limit will be restored the following week. Flexible therapy schedules will also be offered, and patients’ families will be contacted directly by phone to confirm evaluation dates, thus reinforcing treatment adherence [38].

To calculate the sample size, the GRANMO calculator was used *(Sample size and power calculator (v. 7.12.), Institut Municipal d’Investigació Mèdica, Barcelona, Spain)*. Accepting an alpha risk of 0.005 and a beta risk of 0.2 in a one-sided contrast, 23 subjects are required to detect a difference equal to 4.9 points, the minimal clinically important difference of the Fugl-Meyer assessment scores for wrist/hand [39]. Considering a 15% loss, it will be necessary to reach a sample of 21 patients in each group.

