### 2.4. Data Analysis

Parametric tests will be used for the analysis of the results if compliance with the assumptions (normality and equality of variance) and the sample size allow it. These analyses include a Student’s *t*-test for independent or paired samples, ANOVA of one or two factors and repeated measures, and Pearson correlations.

Due to the data nature, analyses will be completed with nonparametric tests such as χ2 and Wilcoxon. The residual effect, period effect, and sequence effect checks will be made.

In all analyses, a confidence level of 0.95 will be adopted. The data analysis will be carried out with the help of the statistical program SPSS 25.0 (SPSS Inc., Chicago, IL, USA).

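### Four co-equal main outcomes tested at 0.05, with no primary outcome, side or visit, and a sample size built on an FMA wrist/hand score that is not a declared endpoint

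*Protocol article*

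**What the plan says.** **Outcomes.** The Abstract begins its list with "The main expected outcomes are changes in the Motricity Index of the Arm (MI), dynamometry of the upper limb" and goes on to FMA-UE and the Stroke Impact Scale. Section 2.3.1 describes the same four as main outcomes, with SIS limited to its hand function domain. None is ranked above the others.

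**Sides and visits.** Section 2.3.1 states: "Due to the bilateral stimulation protocol used, all outcomes will be assessed on both sides". No side is named as primary. Section 2.3 sets a baseline and two later evaluations, one after the rTMS course and one when NeuRow training ends, and singles out neither. The Abstract words the schedule differently, placing the last evaluation 15 days after the last session.

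**Testing level.** Section 2.4: "In all analyses, a confidence level of 0.95 will be adopted". It lists t-tests, one- and two-factor and repeated-measures ANOVA, correlations and nonparametric tests. It gives no order of testing.

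**Sample size.** Section 2.1: "Accepting an alpha risk of 0.005 and a beta risk of 0.2 in a one-sided contrast, 23 subjects are required". The difference is 4.9 points, described as "the minimal clinically important difference of the Fugl-Meyer assessment scores for wrist/hand". The next step reads: "Considering a 15% loss, it will be necessary to reach a sample of 21 patients in each group". No SD is given.

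**FMA as an outcome.** Section 2.3.1 defines FMA-UE as four subscales with a maximum of 66. Wrist (0–10) and hand (0–14) appear only as subscales B and C. The minimal clinically important difference (MCID) "ranges from 4.25 to 7.25 points, depending on the evaluated region of the upper limb".

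**The concern.** A trial that is to support one efficacy conclusion needs one decisive comparison, and its sample size should be calculated for that comparison. Here four measures share top status, two arms are measured and there are two follow-up visits, while every analysis keeps the same 5% error rate. Success could be claimed on whichever measure happens to cross the line.

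The power calculation is also detached from the outcome list. It uses a difference for a wrist/hand score that is not declared as an endpoint, at an alpha that is not the analysis alpha. If the trial ends with mixed results, nothing in the article says which result decides, or which of them had 80% power to be detected.

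**Working it through.** **1. The plan's own figure.** For two means, n per group = 2·SD²·(z₁₋α + z₁₋β)² / Δ². With one-sided alpha 0.005, power 80% and Δ = 4.9, the z-sum is 2.576 + 0.842 = 3.417. No SD is stated, so 23 cannot be reproduced. It can only be solved backwards, SD = 4.9·√(n/2) / 3.417:

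- 23 per group: SD = 4.86
- 23 in total (11.5 per group): SD = 3.44

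The step to 21 per group does not follow on either reading. 23/0.85 = 27.06, which is 28 per group, or 14 per group if 23 is the total. That is a separate defect. It matters here only because 21 × 0.85 = 17.85 evaluable patients per group is then the realistic basis for power.

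**2. Score and alpha.**

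| | Section 2.1 (sizing) | Sections 2.3.1 and 2.4 (analysis) |
|---|---|---|
| Score | FMA wrist/hand; B + C = 10 + 14 = 24 points maximum | FMA-UE, 66 points maximum, plus three other main outcomes |
| Alpha | 0.005 one-sided | 0.05 in all analyses |

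For scale, 4.9/24 = 20% of the wrist/hand range and 4.9/66 = 7% of the total range. These ratios show that the two scores are not interchangeable. They say nothing about power without an SD.

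Power for Δ = 4.9 with 17.85 per group (normal approximation, SDs assumed):

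| SD | one-sided 0.005 | two-sided 0.05 |
|---|---|---|
| 4 | 86% | 96% |
| 5 | 64% | 83% |
| 6 | 45% | 68% |
| 8 | 23% | 45% |

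The answer changes considerably with both the alpha and the SD. The article fixes the first in two ways and the second not at all.

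**3. Family-wise error, independent tests at 0.05:** 1 − 0.95^k.

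- k = 4 (four outcomes, one side, one visit): 1 − 0.8145 = 18.5%
- k = 16 (4 outcomes × 2 sides × 2 visits): 1 − 0.4401 = 56.0%

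**4. Correlated tests.** The outcomes come from the same patients, so independence is too pessimistic. The article gives no correlations, so these are assumed. Simulation: T_i = √ρ·S + √(1−ρ)·e_i, with S and e_i standard normal, 400,000 draws, and at least one |T_i| above 1.96.

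| Tests | ρ = 0 (exact) | ρ = 0.5 | ρ = 0.7 | ρ = 0.9 |
|---|---|---|---|---|
| 4 | 18.5% | 15.6% | 13.0% | 9.3% |
| 16 | 56.0% | 37.6% | 26.4% | 14.6% |

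Even four tests correlated at 0.9 give nearly twice the nominal 5%.

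**5. Keeping all four as primary instead.** Bonferroni gives 0.05/4 = 0.0125 each. A comparison with 80% power at two-sided 0.05 then has about 62%. Over 16 comparisons (0.0031 each) it has about 44%.

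**The case against.** **The count of 16.** A reader might infer that 16 confirmatory tests are planned. The text does not say so. Measuring both sides is not the same as testing both sides. Repeated-measures ANOVA may combine the visits. SIS is a questionnaire and may yield no side-specific score; counted once per visit, it leaves 14 tests. The second evaluation is shorter (60 against 120 minutes), and its content lies in a figure that is not shown. Sixteen is therefore an upper reading only.

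**A false positive is likely.** That would need a rate above one half, and so about 14–16 nearly independent tests (51% for 14). Related motor measures in the same patients are not independent. The supported statement is that the error rate is well above 5%.

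**The powered hypothesis is never tested.** This goes too far. Wrist and hand are subscales of a main outcome, so the data will be collected and could be tested. What stands is that no such test is specified.

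**MCID conflict.** 4.9 lies inside 4.25–7.25, and the article does not assign 7.25 to the total. The two sections do not contradict each other on this.

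**SIS and blinding.** That patients may know their group bears on a patient-reported outcome, but it is a blinding question and forms no part of this point.

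**Left to the SAP.** The choice of adjustment method often is. What stands is that the article itself fixes 0.95 for all analyses, gives four outcomes equal rank, and sizes the trial on a score outside that list. An SAP would have to depart from the article to repair this.

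**The 0.005 as a hidden allowance.** One-sided 0.005 is two-sided 0.01, and four independent tests at that level give 1 − 0.99⁴ = 3.9%. This would answer much of the point if it were the intention, but the article does not say so and section 2.4 does not carry the level into the analysis.

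**Conclusion.** The point holds. No primary outcome, side or time point is named, and every analysis is run at 0.05. If each of the four main outcomes is tested separately on one side at one visit, the family-wise error is 18.5% under independence and about 13–16% at assumed correlations of 0.7–0.5. If both sides and both visits were also tested separately, it would be 26–56% (ρ = 0.7 down to independence), which is an upper bound on what the text allows. The correlations are assumptions, and a common correlation across all tests is a simplification.

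Separately, the stated 80% power refers to a 4.9-point difference in FMA wrist/hand at one-sided 0.005. No declared primary comparison uses that score at that level. The documents do not show that a false positive is more likely than not, nor that the wrist/hand comparison cannot be made.

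**What to change.** 1. In sections 2.3.1 and 2.4, name one primary comparison: the between-group difference in paretic-side FMA wrist/hand (subscales B + C, the score to which the 4.9 points belong) at the final evaluation. Define that evaluation once, reconciling section 2.3 with the Abstract.
2. Use the same alpha, one- or two-sided, in sections 2.1 and 2.4, and state the SD. For orientation, at Δ = 4.9 and 80% power, assumed SDs of 4 / 5 / 6 / 8 need 16 / 25 / 36 / 63 per group before loss at one-sided 0.005, or 11 / 17 / 24 / 42 at two-sided 0.05.
3. If the FMA-UE total is preferred as primary, restate the target difference, SD and power for the total.
4. Make paretic-side Motricity Index, grip strength and SIS secondary, either with Holm adjustment or labelled exploratory. Report non-paretic measurements descriptively.

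With one primary comparison the type I error for the trial's main claim returns to the chosen alpha. Naming it needs no extra visits or measurements, only wording in sections 2.1, 2.3 and 2.4. The cost is fewer outcomes on which confirmatory success can be claimed. Choosing the total also reopens the sample size, and the power statement may become less favourable.

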#### 2.3.2. Secondary Outcomes

Computerized Finger Tapping Task (FTT): The FTT measures motor function and is very sensitive to the slowing down of responses. In this task, following the Strauss application norms, the participants will be instructed to sit comfortably in front of a computer and press the spacebar on the keyboard as fast as possible and repeatedly with the index finger. Five 10 s attempts will be performed with each hand. The average time between two consecutive taps in the five trials will be the dependent variable.

Nine Hole Peg Test (NHPT): The NHPT evaluate the impairment in upper limb dexterity [48]. Patients must pick up as quickly as possible nine pegs from a container one by one unimanually and transfer them into a target pegboard with nine holes until filled. Then, they must return them unimanually to the container. The outcome variable will be the time spent to complete the whole task [49]. The NHPT is considered reliable [50], valid, and sensitive to change [51] among stroke patients.

Modified Ashworth Scale (MAS): The MAS is one of the most used tools for the assessment of spasticity [52]. Patients will be in the supine position with their arms by their side and with their head in a neutral position [53]. The MAS is markedly responsive in detecting the changes in muscle tone in patients with stroke [54]. This scale will be used because secondary changes in spasticity are possible if motor changes are produced.

Nottingham Sensory Assessment (NSA): Somatosensory impairment of the upper limb occurs in approximately 50% of adults after stroke, associated with loss of hand motor function, activity, and participation. The measurement of sensory impairment in the upper limb is a component of rehabilitation that contributes to the selection of sensorimotor techniques that optimize recovery and provide a prognostic estimate of the function of the affected upper limb [55]. There are studies documenting changes produced in the sensation of the upper limb after the application of neurofeedback [56] and even after the intervention with motor imagery [57]. Since the protocol presents an intervention with the application of these techniques, it is possible that there will be changes related to the sensitivity after the use of the platform, NeuRow system (NeuroRehabLab, Funchal, Portugal) [31].

Barthel Index (BI): Accurately assessing the ADLs of stroke patients greatly helps in evaluating the efficacy of stroke treatments [58]. The Barthel Index was originally established to assess ADL in stroke patients and has been used extensively for this purpose [59].

Neurophysiological measurements of cortical plasticity changes:

TMS Resting Motor Threshold (RMT) in the first dorsal interosseous muscle or the abductor pollicis brevis muscle will be recorded to determine the cortical excitability changes and correlate them with the clinical outcomes.

EEG: Different measures of quantitative EEG will be collected. They have been shown to be very useful in evaluating stroke patients’ recovery [60].

### 2.4. Data Analysis

Parametric tests will be used for the analysis of the results if compliance with the assumptions (normality and equality of variance) and the sample size allow it. These analyses include a Student’s *t*-test for independent or paired samples, ANOVA of one or two factors and repeated measures, and Pearson correlations.

Due to the data nature, analyses will be completed with nonparametric tests such as χ2 and Wilcoxon. The residual effect, period effect, and sequence effect checks will be made.

In all analyses, a confidence level of 0.95 will be adopted. The data analysis will be carried out with the help of the statistical program SPSS 25.0 (SPSS Inc., Chicago, IL, USA).

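### None of the tests named for the between-arm comparison adjusts for the baseline value, although every patient has one; a baseline-adjusted model would cost one degree of freedom

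*Protocol article*

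**What the plan says.** Section 2.4 (Data Analysis) makes parametric tests conditional on their assumptions and the sample size. It then names Student's t-test "for independent or paired samples, ANOVA of one or two factors and repeated measures, and Pearson correlations", and adds that "analyses will be completed with nonparametric tests such as χ2 and Wilcoxon". The list is introduced as what the analyses include. It is not tied to any outcome, visit or contrast, and no analysis of covariance, baseline covariate or mixed model is named.

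Section 2.3 states "Three evaluations will be carried out for each patient": one before the intervention, one after the rTMS block and a final one. Section 2.1 admits patients "with a score equal to or greater than 25 according to the Fugl-Meyer Assessment for upper extremity", and section 2.3.1 gives that scale a maximum of 66. Section 1 states the main hypothesis as superiority of BCI-VR training over conventional motor imagery, each added to bilateral rTMS.

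**The concern.** The question is a difference between two randomised arms in a trial of 42 patients. A pre-intervention value of each main outcome is available, and for FMA-UE the entry rule allows anything from 25 to 66. If baseline predicts the final score, leaving it out of the between-arm model costs precision, and any chance imbalance at baseline passes into an unadjusted comparison of final scores. A change score corrects for baseline with a fixed slope of one, which is inefficient when r is moderate.

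Paired within-group tests answer a different question. By section 2.1 both arms receive conventional rehabilitation and bilateral rTMS, so both may well improve. A significant change in one arm and a non-significant one in the other is not evidence that the arms differ.

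**Working it through.** **The plan's own figure.** Section 2.1 sizes the trial at one-sided 0.005 with beta 0.2 and says "23 subjects are required to detect a difference equal to 4.9 points", then "Considering a 15% loss, it will be necessary to reach a sample of 21 patients in each group". No SD is given, so 23 cannot be derived forwards. Solved backwards, if 23 is per arm, SD = 4.9 × √(23/2) / (2.576 + 0.842) = 4.86. The loss step does not reproduce either: 23/0.85 = 27.1, hence 28, not 21. In the other direction, 21 × 0.85 = 17.85, so about 18 evaluable patients per arm, which is the number used below.

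**Inputs.**
- From the article: difference 4.9; 21 per arm less 15%, about 18; confidence level 0.95 (section 2.4), taken as two-sided 0.05.
- Assumed: SD 4.86 (back-solved above) up to 11.84, which is the SD if baseline FMA-UE were uniform over 25 to 66, that is (66 − 25)/√12. Baseline–final correlation r from 0.3 to 0.9. Equal variances at baseline and final evaluation.

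**Formulas.** Effective SD for each between-arm analysis:
- final score: SD
- change score: SD × √(2(1 − r))
- ANCOVA: SD × √(1 − r²)

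The ANCOVA variance relative to the final-score test is 1 − r²: 0.91, 0.75, 0.51 and 0.19 at r = 0.3, 0.5, 0.7 and 0.9. Relative to the change-score test it is (1 + r)/2: 0.65, 0.75, 0.85 and 0.95.

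Power is from the noncentral t distribution with noncentrality 4.9 / (effective SD × √(2/18)), on 34 degrees of freedom, or 33 for ANCOVA. Example at SD 11.84, r = 0.8: change SD = 11.84 × 0.632 = 7.49, noncentrality 1.96; ANCOVA SD = 11.84 × 0.6 = 7.10, noncentrality 2.07.

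**Results** (power in %, differences taken before rounding):

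| SD | r | Final score | Change | ANCOVA | Gain over change |
|---|---|---|---|---|---|
| 4.86 | 0.3 | 83.6 | 70.0 | 86.8 | 16.8 |
| 4.86 | 0.5 | 83.6 | 83.6 | 92.4 | 8.8 |
| 4.86 | 0.9 | 83.6 | 100.0 | 100.0 | 0.0 |
| 6 | 0.3 | 66.3 | 52.1 | 70.3 | 18.2 |
| 8 | 0.5 | 43.1 | 43.1 | 54.0 | 10.9 |
| 8 | 0.7 | 43.1 | 63.5 | 70.5 | 7.0 |
| 11.84 | 0.3 | 22.6 | 17.5 | 24.4 | 6.9 |
| 11.84 | 0.5 | 22.6 | 22.6 | 28.5 | 5.9 |
| 11.84 | 0.8 | 22.6 | 47.9 | 52.0 | 4.0 |
| 11.84 | 0.9 | 22.6 | 76.9 | 78.9 | 2.0 |

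The direction is the same at the alpha used for sizing. With one-sided 0.005, SD 4.86, 18 per arm and the normal approximation, change versus ANCOVA is 49.2 versus 72.4% at r = 0.3, 67.3 versus 82.0% at r = 0.5 and 90.8 versus 95.1% at r = 0.7.

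One small-sample caution: estimating the slope inflates the ANCOVA variance by about 1 + 1/(2 × 18 − 4) = 1.03 on average, which the table leaves out. At r = 0.9 the ratio to the change test then becomes about 0.95 × 1.03 = 0.98, so the advantage there is close to nil.

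**The case against.** The strongest reply is that the plan does use the baseline. Repeated-measures ANOVA and paired tests take it as a time point, and the abstract and section 1 frame the outcomes as changes. That stands. The fair comparator is therefore a change analysis, not a bare final-score test, and against change the gain is small when r is high. A reader might quote the 22.6% power of a final-score t-test as the trial's power. The article nowhere says that final scores will be compared alone, and the figure depends on an assumed SD. There is also a mismatch of scale: section 2.1 takes 4.9 as the important difference for wrist/hand, while the SD of 11.84 belongs to the 66-point total.

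A reader might also infer that the plan drops incomplete patients. Classical repeated-measures ANOVA needs all three visits, but an independent t-test loses only patients without that one score. The article does not say how missing visits are handled, and that may properly be left to an analysis plan that is not shown. Nor does it propose to claim superiority from paired tests; an independent-samples t-test is listed.

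Finally, the list is open-ended and an article condenses. That limits the weight of the point but does not remove it. The section does name its methods, every one is unadjusted, and none is assigned to the randomised contrast. For repeated-measures ANOVA it does not even say which term would be read, and the group main effect averages in the baseline visit, where no treatment effect can exist.

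**Conclusion.** The point holds in a limited form. The named tests leave the baseline unused as a covariate, and the paired ones do not address the hypothesis. A baseline-adjusted comparison was at least as powerful as the final-score and change comparisons at every SD and r tried. The gain over a change comparison is about 0 to 18 points, largest at low r with SD near 6, and 2 to 4 points at SD 11.84 with r 0.8 to 0.9. Over a final-score comparison it runs from under 2 points (SD 11.84, r = 0.3) to about 56 points (SD 11.84, r = 0.9).

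These sizes rest on an SD and a correlation that the article does not give, on equal variances and on 18 evaluable patients per arm. The variance ratios need no SD, but they do depend on r. It would go too far to say that the plan ignores the baseline altogether, or that the existing tests are invalid as between-arm comparisons.

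**What to change.** In section 2.4, or in the analysis plan if one exists, state that for each main outcome the arms are compared at the final evaluation (the third) by a linear model on group and the baseline value of that outcome, reported as an adjusted difference with its 95% CI. Label the paired within-group tests as descriptive.

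If the second evaluation is to be used as well, fit a mixed model with baseline, group, visit and group-by-visit, and take the group contrast at the third evaluation. The interaction and the named contrast are needed. The second evaluation precedes the end of NeuRow training, so a group effect averaged over both visits could dilute the effect of interest. This model also keeps patients who have only one post-baseline visit, which ANCOVA at the final visit alone does not.

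The cost is some rewording and one degree of freedom for the covariate in the basic model, with the same data and the same software. No further covariates and no change to the list of main outcomes are needed for this point.
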